### Outcome measures

On all assessment points, the Dutch versions of the measures described below are included. The administration of the SCID-I and the Y-BOCS during intake will be conducted face-to-face and later assessments are by telephone. Self-report measures will be conducted on paper and are home-based.

#### Primary outcome

The primary outcome of interest for this MCT superiority study is OCD severity at post-treatment, which will be measured with the Y-BOCS [19], a semi-structured interview and the “gold standard” for measuring OCD symptoms. The Y-BOCS is a clinician-ratedsemi-structured interview designed to rate the severity of both obsessions and compulsion. The Y-BOCS consists of 10 items rated 0–4 (range = 0–40). The Y-BOCS has been shown to have good psychometric properties and is sensitive for measuring treatment effects [40]. Further, good internal consistency for both the subscales (obsessions and compulsions) and for the total score of the Y-BOCS has been reported [18].

#### Secondary outcomes

The presence of OCD and co-morbid Axis I diagnosis will be assessed with the Structured Clinical Interview for DSM Axis I Disorders (SCID-I [10]). A recently conducted study with a large sample size (*n* = 151) found adequate to good inter-rater reliability for all Axis I disorders [23]. Secondary outcomes include self-report questionnaires to assess OCD symptoms, co-morbid symptoms, and degree of perceived wellbeing. The Padua-Inventory revised (Padua-IR; [4]) is a self-reportmeasure for OCD severity which consists of 60 items scores on a 0–4 scale (range = 0–240). The Padua-IR has reasonable psychometric properties [40]. The symptom checklist (SCL-90 [8]) is used as a measurement of general psychopathology. The SCL-90 consist of 90 items, all scores from 1 (not at all) to 5 (very much; range = 90–450). This self-report measure has shown good psychometric properties. The Beck Depression Inventory, 2nd version (BDI-II [2]) is included to assess the affective, behavioral, somatic, and motivational components of depression. This frequently used self-report consist of 21 items in the range of 1–4 and has good psychometric properties. Finally, World Health Organization Quality of Life (WHOQOL-Bref [48]) is included and assesses the individuals perception of quality of life with respect to physical health, psychological health, social relationships, and environment. The WHOQOL consists of 26 items which are answered on a 5-point scale. It is concluded that the psychometric properties of this questionnaire are good.

#### Process measures

Changes in both belief domains that have been proposed to be important in the etiology of OCD are assessed. To study changes in metacognitive beliefs about the meaning, significance, and danger of intrusive thoughts, the Thought Fusion Instrument (TFI [45]) will be employed. To study changes in metacognitive beliefs about the necessity of performing rituals in response to obsessions, the Beliefs About Rituals Inventory (BARI [25]) is used. The TFI consists of 14 items and the BARI of 12 items. All items are answered on a 4-point scale in the range of 1–4. There are few data available about the psychometric properties of the TFI and the BARI. Gwilliam et al. [20] found reasonable internal consistency, a moderate test–retest reliability, and some support for the convergent and divergent validity for the TFI. In the developmental phase of this study, the psychometric properties of the TFI and the BARI will be further assessed by our research group.

The Obsessive Belief Questionnaire (OBQ-44 [29]) is included as another measurement with the purpose of the assessment of beliefs considered to be important in the maintenance of OCD. Factor analysis of the scale reveals four factors: (1) perfectionism and intolerance of uncertainty; (2) importance and control of thoughts; (3) responsibility; and (4) overestimation of treat [28]. The OBQ-44 consists of 44 items answered on a scale of 1–4. The psychometric properties are good.

In addition, on both follow-up assessments, participants will be called by a research assistant, who will ask them to provide responses for the Treatment Change Recording Form (TCRF [38]), which will be used to assess the initiation, termination, or change of any form of therapy, hospital services, support group, self-help program, or medication utilized by the participant since post-treatment.

### Interventions

The interventions will be offered at the Anxiety Disorders Department of PsyQ, at which ERP is already delivered as treatment as usual for OCD. Both manual-driven treatments consist of up to 15 weekly sessions of 45 min duration. Treatment can be terminated earlier, when both patient and therapist agree that treatment goals are completed. A minimum of eight sessions will be managed as criteria for each patient to can be classified as treatment completer in the statistical analysis. Interventions will be delivered by nine staff psychologists, who are trained in CBT and who are familiar with the provision of ERP for OCD. Four of the participating therapists were trained by [name] and [name], experts in the field of MCT, preceding the start of a pilot study into the efficacy of MCT for OCD in which they participated as therapists [39]. The other five therapists will be trained in the provision of MCT for OCD by the fourth author (CH) preceding the start of this study. During the study, therapists will be supervised monthly by the fourth author (CH) in separate group sessions for ERP and MCT. In these 1-h supervision meetings, all current cases and therapy notes will be reviewed to ensure treatment quality and adherence. Treatment integrity will also be evaluated by means of randomly assessing recordings of treatment sessions against a session-by-session intervention checklist.

For the purpose of this study we will use an ERP protocol based on the inhibitory learning model of extinction [7], which states that the original fear conditioning is not erased during exposure therapy but stays intact while a second conditioning is developed. Translated to clinical practice, this means that during exposure and response prevention exercises, attention is focused on the disconfirmation of fear cognitions. Before exposure exercises, the fear cognitions are recorded and the exposure is introduced as a way to collect evidence for or against these appraisals. The ERP manual consists of three phases. In the first phase, an explanation of the behavioral model of OCD and rationale is discussed and an anxiety hierarchy containing all of the anxiety provoking situations is developed. The second phase includes both within-session and between-session in vivo and imaginal exposure-exercises, with early exposure to moderately distressing situations with progression toward more anxiety evoking ones. This latter is done to minimalize drop-out in the first exposure and response prevention sessions. Later, the patient is asked to practice in many different situations and circumstances and even alternate between the more easy and difficult exercises. According to the inhibitory learning model, the more variability is added throughout exposure exercises, the better the new information can be retrieved at a later point which minimize relapse [7]. Ritual prevention includes instructions to refrain from all compulsive behaviors. In the final phase, a relapse prevention plan is developed.

MCT focuses exclusively on modifying metacognitive beliefs about intrusive thoughts and the necessity of performing rituals [12]. MCT consists four treatment phases. Phase 1 involves psycho-education about the metacognitive model, increasing patients’ awareness of the role of metacognitions and generation of an idiosyncratic case conceptualization. This is accomplished by eliciting metacognitive beliefs, e.g. by guided questioning. Experiments are used to illustrate maladaptive coping strategies, e.g. the thought suppression experiment in which the patient is asked to suppress the thought of a white rabbit which is rarely completely successful [41]. Also, detached mindfulness (DM) is practiced. In DM, patients are asked to be aware of their intrusive thoughts and try to stop or disconnect any response to that thought, like engaging with their obsessional thoughts by worrying about consequences or the chance of occurrence [44]. Instead, patients practice with evaluating their intrusions and notice them as “just mental events in the mind,” e.g. by visualizing the thought moving away from them. In the second phase, metacognitive beliefs about intrusions are targeted by verbal cognitive restructuring (e.g. questioning the evidence and searching for counterevidence) and behavioral experiments. An example of such an experiment is exposure and response commission (ERC), in which patients are asked to perform rituals and to keep their intrusive thought in mind at the same time, instead of trying to get rid of the intrusive thought. The main aim of ERC is to enable patients to experience obsessive thoughts on a meta-level by obtaining distance from them and discovering that they are unimportant events in the mind [44]. In phase 3, metacognitive beliefs about rituals are challenged, again by means of both verbal methods (e.g. questioning the evidence and an advantages–disadvantages analysis) and behavioral experiments, such as ritual modulation experiments in which patients are asked to alternate between more and less ritual behavior with the aim of assessing its impact on daily life. In the final phase, the therapist and patient work on a relapse prevention plan consisting of a new plan for reacting in response to intrusive experiences combined with a blueprint of the therapy. The old versus new plan consists of attentional strategies and coping behaviors opposite to the strategies and behaviors of the old plan (e.g. applying detached mindfulness [new plan] instead of worrying about intrusions [old plan]). In addition, a blueprint of the therapy is developed, consisting of a summary of the therapy, the case conceptualization, a list of metacognitive beliefs and an overview of evidence challenging them. An overview of the both treatments is provided in Table 1. The full manuals (in Dutch) are available from the corresponding author upon request.

**Table 1 Tab1:** Overview of metacognitive therapy (MCT; [39]; based on [44]) and exposure and response prevention (ERP) for obsessive-compulsive disorder (OCD)

Phase	MCT		ERP	
	Interventions	Sessions	Interventions	Sessions
1	- Provide treatment overview	1–2	- Provide treatment overview	1–3
	- Psycho-education about the metacognitive model of OCD		- Psycho-education about the behavioral model of OCD	
	- Elicit metacognitions by guided questioning		- Generation of a hierarchy of anxiety-provoking situations and avoidance behaviors	
	- Practicing of detached mindfulness			
2	- Modifying metacognitions about intrusions by verbal methods (e.g. questioning the evidence) and behavioral experiments (e.g. exposure with response commission, ritual postponement, and exposure and response prevention experiments)	3–8	- Exposure and response prevention exercises, both within-session and between sessions	4–13
3	- Modifying metacognitions about the necessity of rituals by verbal methods (e.g. questioning the evidence, advantages–disadvantages analysis of performing rituals) and behavioral experiments (e.g. ritual modulation experiments)	9–12	- Generation of a treatment summary consisting of an overview of OCD complaints pretreatment, rest symptoms at post-treatment, and a relapse prevention plan containing helpful interventions to maintain	14–15
4	Generation of a new plan for processing in response to unwanted thoughts, feelings, or events and a therapy blueprint consisting of the case conceptualization, a list of metacognitive beliefs and an overview of evidence challenging them	13–15		

### Statistical analysis

#### Outcomes

Data will be analyzed using SPSS for Windows version 25.

Because of the expected drop-out and the uneven time intervals between measurements (post-test 6-month–30-month follow-up), the use of mixed models is the most appropriate statistical method [36]. This methodology is very suitable to analyze repeated measures by taking dependency between observation into account and the ability to handle missing data. In case of Missing At Random (MAR), we will use these variable(s) as covariate in our analysis. In case of Missing Not At Random (MNAR) we will use pattern mixture models. Mixed models will be adjusted by the baseline values of the repeated measures. Descriptives for means and proportions of baseline clinical and demographic variables between treatment conditions will be reported so potential magnitudes of imbalances can be assessed. Model diagnostics will be assessed by exploring residual plots. In case they are not acceptable, we will apply bootstrapping procedures with the use of R (R core team, 2018).

Fixed effects in our model will be time, treatment, and their interaction. In case of missingness, we will add these variable(s) also as fixed effects. The Benjamini–Hochberg procedure is applied to the significances of the time*treatment interaction *p*-values (two-sided *p* < 0.05) of the different outcome measures. The time variable will be treated categorically, with the first post-baseline measurement as the reference category. To accommodate the modeling of correlation among repeated measurements, we impose a first order autoregressive (AR (1)) structure on the residuals. Next, the interaction effect between time and group will be explored by analyzing the estimated marginal means at different time points. We expect a significant interaction effect between time and group, which means that scores change differently over time in the two treatment conditions. More specifically, we expect a more negative time trend for MCT than for ERP, indicating that the measurement scores in the MCT condition decline more over time than in the ERP condition. To gain further insight into the statistical significance of the improvements achieved in the two treatment conditions, we will perform a least significant difference test with the estimated marginal means to compare changes between treatment conditions. In accordance with the linear mixed models, we expect a statistically significant decline in both treatment conditions between pretest and post-test, but no statistical differences between post-test and both follow-up measures. To allow for comparison with other studies into the effectiveness of ERP and MCT for OCD, Cohen’s *d* statistic ((mean 1 – mean 2) / pooled SD) will be employed to calculate within-group effect sizes (ES) for changes on outcome measures and to evaluate between-group differences. We will calculate Cohen’s *d* statistics for both intent-to-treat samples by using multilevel analysis with all available data and completer samples (our primary analysis: minimum of eight treatment sessions and no change in medication during treatment will be managed as criteria for each patient to can be classified as treatment completer). Based on previous research, we expect a large within-treatment ES for both treatment conditions (Cohen’s *d* > 0.8). We expect a medium between-group ES in favor of MCT. In addition, the clinical significance of treatment effects and amount of drop-out will be examined also to gain further insight into the clinical value of the two treatment conditions.

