### Sample size

There are no studies available directly comparing ERP with MCT. We chose to design our study with enough statistical power to enable us to detect a medium between-group effect (Cohen’s *d* = 0.5 [6]) from baseline to post-treatment. We chose for this medium between-group effect because expecting a larger difference between the two treatment groups does seem unrealistic since numerous studies have found statistically significant change and large improvements in OCD symptoms after ERP. On the other hand, designing our study to enable us to detect a small between-group effect is of less relevance for clinical practice. We used the statistical method presented by Liu and Liang [22] for sample size calculations for studies with correlated observations. To achieve a power of 0.80 with four measurement points with a correlation of 0.5 between repeated measures (standard value) and to detect a medium effect size (Cohen’s *d* = 0.50) between the two treatment conditions over time on the primary outcome measure, severity of OCD symptoms, and an expected drop-out rate of 20%, the minimal sample size necessary in each condition is 50.

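### The missing-data rule picks the model by whether missingness is MAR or MNAR, which observed data cannot show, and it does not limit the added covariates to baseline variables

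*Protocol article*

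**What the plan says.** The endpoint is fixed in the Primary outcome subsection: "The primary outcome of interest for this MCT superiority study is OCD severity at post-treatment". The Outcomes subsection of the statistical analysis then gives the core model: "Fixed effects in our model will be time, treatment, and their interaction". Baseline enters as well: "Mixed models will be adjusted by the baseline values of the repeated measures".

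The treatment of missing data is a two-way branch. One side reads "In case of Missing At Random (MAR), we will use these variable(s) as covariate in our analysis". The other reads "In case of Missing Not At Random (MNAR) we will use pattern mixture models". The following paragraph returns to the first side: "In case of missingness, we will add these variable(s) also as fixed effects".

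The article gives no criterion for deciding which branch applies. It names neither branch as primary and does not call the pattern-mixture model a sensitivity analysis. The variables to be added are not named, and nothing confines them to baseline. Drop-out is allowed for in the Sample size section: "an expected drop-out rate of 20%, the minimal sample size necessary in each condition is 50".

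**The concern.** Data can show that missingness is related to something observed, which is evidence against missing completely at random. They cannot show whether, given everything observed, it also depends on the unseen values. For any MNAR model there is a MAR model that fits the observed data equally well. A rule that switches models on this distinction therefore has a condition that nobody can evaluate, and whoever applies it must use judgement with the data available. The MNAR branch is also not one analysis: a pattern-mixture model needs an identifying restriction that the data cannot check, and none is stated.

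The covariate branch carries a second risk. Adjusting for baseline predictors of missingness is sound and makes MAR more credible. Adjusting for something that happens after randomisation is different. Sessions attended is the clearest example: it may well predict a missing assessment, and it can be a consequence of treatment. The Interventions section lets treatment stop early once goals are met, so a low count can reflect either a good response or drop-out. As a fixed effect it would make the comparison of metacognitive therapy (MCT) with exposure and response prevention (ERP) conditional on a result of treatment.

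**Working it through.** **The plan's own figure.** Inputs from the Sample size section: d = 0.50, power 0.80, four measurements, correlation 0.5, drop-out 20%. That section gives no alpha; two-sided 0.05 is assumed, as the Outcomes subsection uses for the interaction tests.

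- n per arm = 2(1.960 + 0.842)² / 0.50² × [1 + (4 − 1) × 0.5] / 4 = 62.79 × 0.625 = 39.24, rounded up to 40.
- With drop-out: 40 / (1 − 0.20) = 50 per arm, as stated.

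So the planned N is not in question. The calculation allows for 10 of 50 patients lost in each arm.

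**How far the choice of model can move the contrast.** Let p be the proportion with a missing post-treatment Y-BOCS, and δ the amount in SD by which those patients are worse than MAR predicts. The pattern-mixture contrast differs from the MAR contrast by

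shift = p(ERP) × δ(ERP) − p(MCT) × δ(MCT).

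The documents give no δ; the values below are assumptions.

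| Scenario | δ = 0.25 | δ = 0.5 | δ = 1.0 |
|---|---|---|---|
| 20% missing, δ in ERP arm only | 0.05 | 0.10 | 0.20 |
| 20% missing in both arms, same δ | 0 | 0 | 0 |
| 10% missing in MCT, 30% in ERP, same δ | 0.05 | 0.10 | 0.20 |

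The first row is 0.20 × δ, or 10%, 20% and 40% of the design effect of 0.50. The third is (0.30 − 0.10) × δ; its unequal rates are also an assumption.

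**Scale against sampling error.** For a single unadjusted comparison the standard error is √(2/40) = 0.22 SD with 40 per arm and √(2/50) = 0.20 SD with 50. A shift of 0.10 SD is thus about half a standard error.

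**Worst case for a free choice.** A simulation (400,000 replicates) took 50 per arm, a 20% chance of a missing score in each arm, no difference among observed patients and a two-sided 5% test. It counted a result as significant if either the MAR or the pattern-mixture test was.

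- Same δ in both arms: rejection in 0.054, 0.058 and 0.066 of trials for δ = 0.25, 0.5 and 1.0.
- δ in the ERP arm only: 0.066, 0.089 and 0.160.
- The MAR test alone stays at 0.050.

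In the one-arm case most of the rise comes from the assumed shift: the pattern-mixture test alone rejects in 0.055, 0.073 and 0.138. The figures bound the harm and do not predict it.

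**The case against.** The best defence is that the authors meant the usual arrangement, a MAR mixed model with a pattern-mixture check, and that the covariate list and its timing belong in an analysis plan that is not shown. The second part has force for the list itself. It does not rescue the rule. An analysis plan could add detail, but it could not make an untestable condition testable; it would have to replace the branch.

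Several objections limit the size, and they stand:

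- **Drop-out is not the same as a missing outcome.** The Design section undertakes to assess patients who leave treatment where this can be done. The missing fraction may therefore be below 20%.
- **The completer label.** The Outcomes subsection, in the sentence on Cohen's d, refers to "completer samples (our primary analysis: minimum of eight treatment sessions and no change in medication during treatment". In that set a medication change cannot serve as a covariate, because nobody has one, and sessions run only from 8 to 15. Fewer scores would be missing there. The label fixes an analysis set and not a missing-data model, and a completer can still miss an assessment, so the branch remains.
- **Symmetry.** With equal drop-out and equal δ the shift is zero.

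A reader might also infer more than the documents support:

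- **That 20 to 30% drop-out is expected.** The plan expects 20%. The figure of about 30% comes from the Background, concerns ERP only, and counts refusers together with drop-outs.
- **That early response could become a covariate for the primary endpoint.** No outcome is scheduled between baseline and post-treatment, and baseline is already in the model.
- **That the model will be chosen after unblinding.** The article does not say when the choice is made, by whom, or whether that person is blinded.

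**Conclusion.** The point holds as a rule that is badly fixed, not as a missing detail. The model is made to depend on a distinction that observed data cannot settle, and the added fixed effects are not limited to baseline. The text does not say that a post-randomisation covariate will be used; it only fails to exclude one.

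The size is conditional. At 20% missing, with δ between 0.25 and 1.0 SD in one arm only, the contrast moves by 0.05 to 0.20 SD against 0.50. The 20% is an upper guide and the δ range is assumed. The movement is nil when drop-out and shift match across arms. It would be tempting to say that the choice of model can reverse the trial's conclusion. The figures show only that a shift of about half a standard error could tip a borderline result. The correction should be made, but the design and the planned N do not depend on it.

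**What to change.** Replace the branch with three statements:

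1. In whichever analysis set is designated primary, the likelihood-based mixed model under MAR is the single primary model. It includes baseline Y-BOCS and a short list of baseline covariates fixed before outcome data are examined.
2. A pattern-mixture (delta-shift) model is always run as a sensitivity analysis, over a stated range of δ set separately by arm, whatever the missingness looks like.
3. Only baseline variables may be added as fixed effects. Post-randomisation predictors of missingness may enter an imputation model only.

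Whether the primary set should be completers or all randomised patients is a separate question, which this change leaves open. The cost is a few sentences and one extra sensitivity analysis. N stays at 50 per arm. The Trial status section reports 68 patients randomised and recruitment still open, so at that stage inclusion had not closed.

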So far, there is preliminary evidence supporting the efficacy of MCT for OCD. The clinical significance of treatment effects in the following mentioned studies is calculated using the standard criteria developed by Fisher and Wells [11, 14], based on the method of Jacobson and Truax [21]. Based on these criteria, patients are classified as recovered if they achieved a reduction of minimal 10 points on the Yale-Brown Obsessive Compulsive Scale (Y-BOCS [19]; a semi-structured interview for OCS) and a post-treatment score < 14. When achieving a post-treatment score < 7, patients are classified as asymptomatic. Using single case methodology, Fisher and Wells [12] found clinically significant improvements for four OCD patients with different clinical presentations who were treated individually with MCT. Two of the four participants were asymptomatic at both post-treatment and three-monthfollow-up assessments. Furthermore, Rees and Van Koesveld [33] found that seven out of eight participants in an open trial of group MCT for OCD reached criteria for a recovery status on the Y-BOCS at three-monthfollow-up (87.5%). In an additional study, Fitt and Rees [16] found similar clinically significant reductions among three patients treated with MCT using videoconference. In an open trial of individual metacognitive therapy among 25 patients with OCD, Van der Heiden et al. [39] found statistically significant reductions on all outcome variables. Moreover, in terms of clinically significant results, 74% of the treatment completers (*n* = 19) were classified as recovered after treatment and 47% as asymptomatic. At follow-up, this increased to 80% and 67% respectively. Finally, Simons et al. [35] found positive outcomes of MCT in comparison to ERP in the treatment of pediatric OCD in a case series design. Together, these findings suggest that MCT might be an efficacious treatment for OCD and deserves controlled evaluation. The present trial has been initiated to compare the relative efficacy of MCT with ERP, in an outpatient clinical sample of patients with OCD. Our main hypothesis is that MCT is more efficacious than ERP in the treatment of OCD in terms of both statistically and clinically significant improvements, both directly after treatment (primary outcome) and at follow-up.

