**Fig. 3 Fig3:**
[figure not shown]
Standard protocol Items: Recommendations for Interventional Trials (SPIRIT). Diagram of enrolment, interventions and assessments over time. MCT metacognitive therapy, ERP exposure and response prevention, SCID-I Structured Clinical Interview for DSM Axis I Disorders. Primary outcome measure: Yale-Brown Obsessive Compulsive Scale (Y-BOCS). *Secondary outcomes: Padua Inventory-Revised (Padua IR); The Symptom Checklist (SCL-90); The Beck Depression Inventory, 2nd version (BDI-II); World Health Organization Quality of Life (WHOQOL-Bref); Obsessive Belief Questionnaire (OBQ-44). **Process measures: Thought Fusion Instrument (TFI); and Beliefs About Rituals Inventory (BARI)

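### The Benjamini–Hochberg correction is put on interaction p-values without setting the single primary outcome apart, while the treatment contrasts at each visit are left unadjusted

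*Protocol article*

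**What the plan says.** Under Primary outcome, the protocol article singles out one measure at one time: "The primary outcome of interest for this MCT superiority study is OCD severity at post-treatment, which will be measured with the Y-BOCS". The main hypothesis, at the end of the section on metacognitive treatment, extends the superiority claim over time: "both directly after treatment (primary outcome) and at follow-up".

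The Sample size section plans 80% power "to detect a medium effect size (Cohen’s *d* = 0.50) between the two treatment conditions over time on the primary outcome measure". It uses four measurements, a correlation of 0.5 and 20% drop-out, and arrives at 50 per arm. It gives no alpha and mentions no allowance for multiple testing.

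Under Statistical analysis, Outcomes, the multiplicity rule reads "The Benjamini–Hochberg procedure is applied to the significances of the time*treatment interaction" p-values of the various outcome measures, at a two-sided 0.05 level. Y-BOCS is neither exempted nor given priority, and the members of the family are not listed. In the same section, baseline enters as an adjustment, and time is categorical with the first post-baseline visit as reference. The authors say that they expect the interaction to be significant. For the treatment comparison itself, "we will perform a least significant difference test with the estimated marginal means to compare changes between treatment conditions".

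One instrument is classed in two ways. The Fig. 3 legend lists "Obsessive Belief Questionnaire (OBQ-44") among the secondary outcomes. The text places it under Process measures: "The Obsessive Belief Questionnaire (OBQ-44 [29]) is included as another measurement".

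**The concern.** A single pre-declared primary test needs no multiplicity correction. Inside a Benjamini–Hochberg family of K measures, the threshold that Y-BOCS must meet moves between 0.05/K and 0.05 according to how the other measures turn out. The verdict on the primary outcome could then hang on self-report scales, in a trial sized as if Y-BOCS stood alone.

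The correction is also attached to the interaction, whereas superiority at post-treatment and at follow-up is a statement about treatment differences at given visits. Least significant difference applies no correction to those differences. The two problems concern different p-values, so which one bites depends on which p-value decides the trial. The protocol does not settle that.

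**Working it through.** **1. Reproduce the sample size.** Inputs from the Sample size section: d = 0.5, m = 4 measurements, ρ = 0.5, power 0.80, drop-out 20%. Alpha is assumed to be two-sided 0.05. The method for correlated observations, as a time-averaged difference, gives

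n = 2(1.960 + 0.842)² × [1 + (m − 1)ρ] / (m d²) = 2 × 7.849 × 2.5 / (4 × 0.25) = 39.24, so 40 per arm.

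40 / 0.80 = 50 per arm, which is the stated figure. A one-sided 0.05 gives 30.9 before drop-out and does not match. The strictest Benjamini–Hochberg thresholds do not match either: 0.05/6 gives 61 before and 77 after drop-out, and 0.05/8 gives 64 and 80. The plan therefore corresponds to one unadjusted two-sided 0.05 test.

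**2. Reading A: the interaction p-value decides.** Take the planned strength of evidence as given and ask what the family costs. With 40 evaluable per arm, the expected z is 0.5 / √(0.625 × 2/40) = 2.83, and power at 0.05 is Φ(2.83 − 1.96) = 0.81.

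The family size is an assumption. It is 6 for Y-BOCS plus the five secondary measures in the Fig. 3 legend, and 8 if TFI and BARI are added. If no other measure is rejected, the threshold and power are:

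- K = 6: 0.05/6 = 0.0083, power Φ(2.83 − 2.64) = 0.575
- K = 8: 0.05/8 = 0.00625, power Φ(2.83 − 2.73) = 0.537

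Simulating the full procedure (K = 6 or 8, inter-measure correlation 0.3 or 0.5) gives:

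| Effect on the other measures | Power for Y-BOCS |
|---|---|
| Same as Y-BOCS | 0.75–0.77 |
| Half of Y-BOCS | 0.59–0.63 |
| None | 0.54–0.58 |
| Y-BOCS tested alone | 0.81 |

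**3. Reading B: the post-treatment contrast decides.** With baseline as covariate and post-treatment as reference time, the treatment coefficient is the post-treatment difference. The interaction terms are the 6-month and 30-month differences minus that difference. If d = 0.5 holds at all three post-baseline visits, the interaction null is true and it is rejected at a rate of 0.05. The post-treatment contrast has variance factor 1 − 0.5² = 0.75 and expected z 0.5 / √(0.75 × 2/40) = 2.58, so power is 0.73. It pays no penalty, because it is not in the corrected family.

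The uncorrected contrasts number up to 8 measures × 3 visits = 24. With all nulls true:

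- independent tests: 1 − 0.95²⁴ = 0.71
- without the Y-BOCS post-treatment contrast, which needs no correction: 1 − 0.95²³ = 0.69
- all 24, simulated with inter-measure correlation 0.3–0.5 and first-order autoregressive correlation 0.5 between visits: 0.54–0.62

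**4. Family membership.** If process measures are outside the family, the class of OBQ-44 decides whether it enters, and so changes K and every threshold. If all eight measures are pooled, its label makes no difference.

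**The case against.** A reader might infer that the correction cuts the power of the baseline-adjusted post-treatment contrast from 0.73 to about 0.44. The document does not support that. It attaches the correction to interaction p-values only, so the test with power 0.73 is not in the family. The 0.44 would also need a true medium effect on Y-BOCS and none on any other measure, including the Padua-IR, which also measures OCD severity. If the other measures respond as strongly as Y-BOCS, the loss under Reading A is only about 4–6 points.

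It is also fair to say that keeping the primary in the family is conservative. Its threshold never exceeds 0.05, so no false claim for Y-BOCS is added and the harm is lost efficiency.

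The 0.71 is an independence bound and should not be the headline. The contrasts are introduced as a follow-up to the interaction. If they were read only where the corrected interaction is significant, the familywise rate would be about 0.04 under the same assumed correlations. No such gate is stated, so this softens the concern without removing it.

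Listing the family can be left to a fuller document. The absence of a list is not the point here. The points are the stated rule, which does not set the primary apart, and the two conflicting labels for OBQ-44.

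The authors read the interaction as a steeper decline under MCT, which favours Reading A. The stated baseline adjustment and reference category favour Reading B. The text does not resolve this.

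**Conclusion.** The point holds as a misplaced correction that should be repaired. It does not show that the primary analysis is invalid. Under Reading A, the primary loses about 4–6 points of power if all measures move together and up to about 27 points if only Y-BOCS moves. Under Reading B, the primary loses nothing to the correction, but the correction answers a different question from the hypothesis, and the secondary and follow-up contrasts have no stated error control.

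These sizes rest on an alpha of two-sided 0.05 for the sample size, a family of 6–8, equal inter-measure correlations of 0.3–0.5 and, for the false-positive rate, a between-visit correlation of 0.5. The Reading A figures carry over the protocol's own sizing basis, a time-averaged difference. They do not give the power of the interaction as coded, which could be far lower.

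**What to change.** State that the Y-BOCS treatment contrast at post-treatment is the sole primary test, at two-sided 0.05, outside the Benjamini–Hochberg family. Apply the correction to the treatment contrasts of the secondary outcomes and the follow-up visits in place of the interaction terms, or label those contrasts exploratory. Assign OBQ-44 to one class, the same in the Fig. 3 legend and in the text.

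This takes a few sentences. Multiplicity gives no reason to change the 50 per arm. The price is somewhat stricter secondary claims. The 0.73 for the post-treatment contrast (40 evaluable per arm, correlation 0.5) against the planned 0.80 arises from sizing on an average over four measurements. It is not a cost of this change.
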